## Data collection and management and confidentiality

### Plans for assessment and collection of outcomes {18a}, Data management {19}, Confidentiality {27}, Plans for collection, laboratory evaluation and storage of biological specimens for genetic or molecular analysis in this trial/future use {33}

The assessment of outcomes will be carried out at the 1st Department of Cardiology, Medical University of Warsaw, while the rehabilitation will be conducted according to a scheduled program. An experienced cardiologist familiar with the study protocol will conduct all the control visits, which will take place in the cardiac ambulatory clinic. Blood samples will be sent to the local laboratory. All blood samples will be tested in the laboratory according to the locally implemented standards and subsequently utilized. There are no plans for future blood use. No other biological specimen will be tested during this trial. Patients will be asked to fulfill the MacNew, EQ-5D-5L, and DASS21 questionnaires. The highest data quality is one of the authors’ primary goals while conducting a trial. Every information will be entered into a database and subsequently checked by another investigator. Every investigator will have a valid good clinical practice certificate.

All data collected during the study and medical documents will be protected and stored in a room dedicated to clinical trial records. All electronic materials will be duly stored in the principal researcher’s computer protected with a password known only to the principal researcher. Additionally, a backup in the cloud will be performed after new data collection.

The highest level of confidentiality will be applied. The participants’ data will be kept separately from any identifying information. According to good clinical practice, all investigators will make every effort to keep the sensitive data confidential.

## Statistical methods

### Statistical methods for primary and secondary outcomes {20a}, Methods for additional analyses (e.g. subgroup analyses) {20b}, Methods in analysis to handle protocol non-adherence and any statistical methods to handle missing data {20c}, Interim analyses {21b}

In terms of the endpoints, we will look at the frequency of the events 6 months after the discharge, since we believe that due to randomization the groups will be similar at the beginning. No other (including no interim) analyses will be performed in the present study. Regarding secondary endpoints, the change from baseline will be assessed and the frequency of the events in case of rehospitalizations and/or urgent ambulatory visits after 1 month. The distribution of continuous variables will be estimated using the Shapiro-Wilk test. Continuous variables presented with normal distribution will be presented as mean values and standard deviations (SD). All continuous variables presented non-normal distribution will be demonstrated as median values and interquartile ranges. In the case of variables with a normal and non-normal distribution, the groups will be compared using the Student's t-test and the non-parametric Mann-Whitney U test. The comparison of qualitative variables between the groups will be performed using the Fisher exact test. In order to compare changes in the values of continuous variables over time, the analysis of variance will be performed. To compare the outcome of the patients, the Kaplan-Meier estimators will be utilized. For quantitative variables, the change from baseline will be assessed. Additionally, in order to diminish differences in sex and age related to group size, propensity score matching analysis will be performed as well. We also plan to conduct a subanalysis in the group of patients who attended rehabilitation, as well as in those who did not attend.

A per-protocol analysis will be performed after completing all of the follow-up visits. In the analysis, we will include all patients who meet inclusion criteria and sign informed consent regardless of the follow-up completion. Statistical calculations will be performed twice; after obtaining data from the first follow-up visit from all patients and after the final follow-up, 6 months after discharge. In case of missing data, patients will be excluded from the particular analysis.

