### Sample size {14}

Currently, data regarding the achieved reduction of rehospitalizations or prelevance of urgent visits associated with mobile application use remains limited. Most previous studies were conducted on smaller populations. The sample calculation was based on Widmer and colleagues’ [5] study, considering rehospitalization and urgent ambulatory visits—comparing the effects of an online and smartphone-based program with standard rehabilitation on the mentioned endpoint. A 40% decrease in the primary endpoint was observed. Fifty percent of patients in the control group and 20% in the interventional arm were rehospitalized or visited the emergency department.

An online calculator (https://clincalc.com/) was used to determine the sample size, assuming the power of 80% and significance of 5%. A total of 76 patients (38 per group) were required. However, considering a possible lost-to-follow-up group and possible dropouts, a decision to recruit 100 patients was made. The reason for the dropout is lack of consent or inability to attend control visits or consent withdrawal.

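### Continuous secondary outcomes with a recorded baseline are planned as change scores with a test chosen by Shapiro-Wilk; one prespecified baseline-adjusted model would be more precise and would fix the effect measure

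*Protocol article*

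**What the plan says.** All the relevant statements are in the protocol article, under the statistical methods heading that covers items {20a} to {21b}.

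- For secondary endpoints: "Regarding secondary endpoints, the change from baseline will be assessed". The same section says again: "For quantitative variables, the change from baseline will be assessed".
- For choosing the test: "The distribution of continuous variables will be estimated using the Shapiro-Wilk test". Variables judged normal go to Student's t-test between groups, the others to the Mann-Whitney U test.
- For the time course: "In order to compare changes in the values of continuous variables over time, the analysis of variance will be performed".

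No baseline covariate is named. A propensity-score matched analysis on sex and age is added.

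The section on secondary outcome measures shows which baselines exist. Weight is taken on admission, and cholesterol is measured during the hospital stay. Blood pressure is a five-day home average before each control visit, with no matching value before discharge. The text shown gives no baseline timing for the questionnaires, and the timeline figure is not available.

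**The concern.** The hypothesis under Objectives {7} is expressed through risk-factor management and quality of life. The sample size was set for the primary event outcome only, so precision on the continuous outcomes depends on how they are analysed.

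Two features of the stated method work against them.

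1. **Precision.** A change score subtracts the whole baseline value, as if the regression of follow-up on baseline had slope 1. With equal SDs the slope equals the correlation, which is below 1. The change score therefore over-corrects and carries extra noise. When the correlation is below 0.5 it is less precise than ignoring the baseline altogether.
2. **Effect measure.** A t-test targets a mean difference and a Mann-Whitney test compares ranks. If a normality test on the trial data decides between them, what will be reported for a given outcome is unknown until the data are seen. The analysis of variance also covers the same variables, and no lead analysis is named.

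**Working it through.** **Inputs from the Sample size {14} section.** The rates assumed are 50% and 20% ("Fifty percent of patients in the control group and 20% in the interventional arm were rehospitalized"), with 80% power and 5% significance (two-sided assumed here). "A total of 76 patients (38 per group) were required"; then "a decision to recruit 100 patients was made", about 50 per arm if balanced.

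**Inputs not in the document, assumed here.** Baseline-to-follow-up correlation r from 0.3 to 0.9; equal SDs at baseline and follow-up; a true effect of 0.5 SD for the power figures.

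**Step 1: the plan's own figure.** With a pooled rate of 0.35,

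n per arm = [1.960 × √(2 × 0.35 × 0.65) + 0.842 × √(0.5 × 0.5 + 0.2 × 0.8)]² / 0.30² = 38.48.

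Rounded up, this is 39 per arm or 78 in total, within two patients of the stated 76. It concerns the primary binary endpoint only, and nothing below changes it. The article gives no design figure for any continuous outcome.

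**Step 2: variances.** The between-arm difference has variance (2/n) × V, with V in units of SD²:

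- change score: V = 2(1 − r)
- ANCOVA: V = (1 − r²) × [1 + 1/(2n − 4)], where the bracket is the price of estimating the slope. At n = 50 it is 1 + 1/96 = 1.0104.

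At r = 0.5, change gives 1.000 and ANCOVA gives 0.75 × 1.0104 = 0.758, a reduction of 24%.

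**Step 3: results at 50 per arm.** The detectable difference at 80% power is (1.960 + 0.842) × √(2/50) × √V = 0.560 × √V.

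| r | V, change | V, ANCOVA | Ratio | Reduction | Detectable difference in SD, change / ANCOVA | Power at 0.5 SD, change / ANCOVA |
|---|---|---|---|---|---|---|
| 0.3 | 1.40 | 0.919 | 0.66 | 34% | 0.66 / 0.54 | 56% / 74% |
| 0.5 | 1.00 | 0.758 | 0.76 | 24% | 0.56 / 0.49 | 70% / 82% |
| 0.7 | 0.60 | 0.515 | 0.86 | 14% | 0.43 / 0.40 | 90% / 94% |
| 0.9 | 0.20 | 0.192 | 0.96 | 4% | 0.251 / 0.246 | about 100% / about 100% |

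Simulation with 4,000 trials per value of r gave variance ratios of 0.66, 0.74, 0.86 and 0.96. At r = 0.5, 50 per arm with ANCOVA is worth 50 × 1.00/0.758 = 66 per arm with change scores.

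**Step 4: how far the assumptions matter.**

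- *Fewer patients.* At 38 per arm and r = 0.5, power for 0.5 SD is 59% with change scores and 71% with ANCOVA.
- *Very high correlation.* At r = 0.99 the ratio is 1.005, so the gain is gone and very slightly reversed.
- *Unequal SDs.* Suppose the follow-up SD of LDL-C were 0.7 of the baseline SD (assumed) and r = 0.5. Then change gives 1 + 0.49 − 2 × 0.5 × 0.7 = 0.79, and ANCOVA, before the 1% slope cost, gives 0.49 × 0.75 = 0.37. The change score has about 2.15 times the variance.

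**The case against.** The strongest reply has four parts.

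1. **The t-test on change scores is inferred.** The section says that groups are compared, and elsewhere that change from baseline is assessed, without tying the two in one sentence. That is fair, but the other reading does not rescue the plan. If the tests were run on the follow-up value alone, V would be 1, and ANCOVA's V at 50 per arm would still be 0.919, 0.758, 0.515 and 0.192 at the four correlations. Nor is this detail merely left to an analysis plan: the article states the analysis variable twice and states the rule for selecting the test.

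2. **The gain rests on unknown quantities.** This stands. The article gives no correlation, SD or effect size for a secondary outcome. Body weight may well correlate at 0.9 or so (an assumption), where the gain is only about 4%.

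3. **Few baselines are documented.** This also stands. Among the continuous outcomes, only weight and cholesterol have an explicit one.

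4. **The plan already addresses chance imbalance by propensity matching.** That uses sex and age, not the outcome's own baseline value, and matching can discard patients.

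A reader might also infer that the fix applies to every outcome. It does not. The primary composite, the 1-month composite and return to work have no baseline value. The risk-factor targets in Table 1 are scored as met or not and compared by Fisher's exact test. Those targets also give LDL-C, BMI, systolic pressure and smoking a fixed binary endpoint, so it would be too strong to say that the risk factors have no defined effect measure. The gap concerns their continuous analyses and the questionnaire scores.

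**Conclusion.** The point holds for continuous secondary outcomes with a recorded baseline, as a matter of efficiency and prespecification. With equal SDs and about 50 per arm, the stated change-score analysis gives up about 34%, 24%, 14% or 4% of variance relative to ANCOVA at assumed correlations of 0.3, 0.5, 0.7 or 0.9. The normality gate separately leaves the choice between a mean and a rank comparison to the data.

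A reader might conclude that the change-score comparison is biased or invalid, or that it ignores the baseline. Neither follows: under randomisation it is unbiased, and it uses the baseline, only with a slope fixed at 1. The required sample size of 76 and the primary analysis are untouched.

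**What to change.** For each continuous secondary outcome with a recorded baseline, name one lead analysis. This covers body weight/BMI and LDL-C, and the questionnaire scores and blood pressure only if a like-for-like baseline is taken.

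- **Model:** either one repeated-measures model for the 1- and 6-month values, with arm, visit, arm-by-visit and the baseline value, or ANCOVA on the 6-month value with arm and baseline. State which. The repeated-measures model replaces the separate analysis of variance and lets a patient with only one control visit contribute.
- **Report:** the adjusted difference at 6 months with its 95% CI. If LDL-C is analysed on the log scale, this is a ratio of geometric means.
- **Test selection:** remove Shapiro-Wilk as the selector. Keep Mann-Whitney as a sensitivity analysis.
- **Scope:** say that this does not apply to the primary composite, the 1-month composite, return to work or the met/not-met endpoints.

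For weight and LDL-C the change is one of wording and needs no new data. It is cheap but not entirely free: one degree of freedom, about 1% variance inflation at 50 per arm, and the usual model assumptions. A patient without a baseline value drops out of ANCOVA under the complete-case rule, but would drop out of a change score as well.

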## Assignment of interventions: allocation, blinding

### Sequence generation {16a}, Concealment mechanism {16b}, Implementation {16c}, Who will be blinded {17a}, Procedure for unblinding if needed {17b}

This is an open-label study. Randomization will be performed with an online tool by an independent statistician available at (www.randomizer.org). A hundred sets will be generated, each with a number (1 for CG and 2 for IG). All allocations to CG and IG will be executed before the study begins. The list of subsequent allocations will not be visible for the recruiting physician until the initial eligibility assessment of the patient and obtaining the patient’s consent for study participation. After collecting the initial documentation, the physician will be unblinded and will receive the group allocation information from the principal investigator. It should be underlined that the person who checks for inclusion criteria and introduces the patient into the trial protocol is blinded until patient agreement. Figure 1 shows the study design flow chart, describing all the steps of the study (Fig. 1). The investigator performing statistical analysis will be blinded, as well as nurses collecting blood samples on the follow-up visits. Taking into consideration the use of the mobile application in everyday practice, it is impossible to blind physicians performing follow-up visits. It could be regarded as ethically doubtful, because based on the data provided via mobile application, clinical decisions can be made (i.e., blood pressure treatment augmentation).

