### Intervention description {11a}, Criteria for discontinuing or modifying allocated interventions {11b}, Strategies to improve adherence to interventions {11c}, Relevant concomitant care permitted or prohibited during the trial {11d}

Patients in the intervention group will be granted access to the mobile application (afterAMI) during the rehabilitation process. Access to the app is what differentiates the groups. afterAMI app offers several features described below. What is more, a dedicated web page will be used by medical professionals to improve everyday clinical work organization and enable better contact with the patients.

Patients in the intervention group will also be given access to educational data about their diseases. Every educational chapter was prepared by a cardiologist experienced in managing patients after MI.

Additionally, every patient will regularly receive messages with notifications about the recommended lifestyle interventions and promoting adherence to the therapy. The notes focus mainly on cardiovascular risk factors and ways of controlling them. We made na effort to emphasize the importance of everyday lifestyle changes in terms of minimizing the risk of potential ischemic events in the future. The role of physical activity and drug adherence was frequently emphasized. All notes were prepared based on recommendations provided by the European Society of Cardiology [11]. An optimal scheme for message quantity and structure has not been described yet in the case of cardiac patients. In a recent meta-analysis, Bashi et al. concluded that the results of mobile application-assisted patient education generally show a positive, promising result. However, due to poor reporting quality and considerable heterogeneity of applied interventions, further studies are required in order to develop a comprehensive, optimal educational scheme [12]. In another paper, a cardiac telerehabilitation program augmented by a short message service (SMS) delivered to patients once a week, resulted in both physical fitness and quality of life improvements [13]. Based on those reports, the authors of this trial decided to send 2 messages weekly. The notifications are also considered as a strategy to improve adherence to the recommendations.

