Additionally, a medical history card will be created for each patient, based on the discharge documents from the hospital. This solution aims for the patient always to have brief information about undergoing coronary interventions. This knowledge might be crucial for the physicians performing subsequent percutaneous coronary interventions (PCI) in the future and could potentially decrease time-to-balloon.

Finally, the application offers a contact panel to text message and call the cardiologists at the hospital. We believe that this will translate into better work organization, better time management (as fewer consultations are likely to be missed by patients), and increased patient safety. All patients randomized to IG will be thoroughly trained in application features and capabilities before discharge.

On the contrary, patients randomized to the CG will be provided with the best available care, based on current guidelines and standards of care [15]. What is more, all patients will be provided with intense medical care supervision, as every patient included in the study will have two additional cardiological consultations.

Rehabilitation programs are recommended for every patient hospitalized due to MI. It has been underlined, that it improves a patient’s prognosis. However, the final decision on the participation is up to the patient. It should be noted, that the study is carried out during the COVID-19 pandemic. Some patients are refusing to participate in the rehabilitation program in fear of infection. However, owing to the randomization, the number of patients who refused to attend rehabilitation is expected to be similar between the groups. Rehabilitation programs include regular cardiac consultations with an experienced physician, psychological sessions, exercise training, stress management programs, and dietary recommendations. The patient is offered versatile support for one year after MI. Patients who refuse to take part in the rehabilitation program are managed by a general practitioner. Owing to the randomization, patients’ distribution is expected to be similar in both groups.

All data implemented into the application was prepared by experienced cardiologists with considerable experience in both, clinical practice as well as eHealth use.

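### Two added analyses, propensity-score matching on sex and age and a split by rehabilitation attendance, are weaker than available alternatives; the main unmatched comparison is not affected

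*Protocol article*

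**What the plan says.** The Statistical methods section ({20a} to {20c}) compares event frequency between the arms at 6 months and uses Fisher's exact test for categorical variables. It then adds two analyses:

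- Matching: "in order to diminish differences in sex and age related to group size, propensity score matching analysis will be performed as well".
- Attendance split: "We also plan to conduct a subanalysis in the group of patients who attended rehabilitation, as well as in those who did not attend".

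Other sections bear on the second analysis:

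- Intervention description: rehabilitation is recommended to every patient, but "the final decision on the participation is up to the patient". The section then states that "owing to the randomization, the number of patients who refused to attend rehabilitation is expected to be similar between the groups".
- Same section, on timing: "All patients randomized to IG will be thoroughly trained in application features and capabilities before discharge". Allocation is therefore known before the patient leaves hospital.
- Same section, on the twice-weekly app messages: "The notifications are also considered as a strategy to improve adherence to the recommendations".
- Assignment of interventions: "This is an open-label study".

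**The concern.** **Matching.** Propensity-score matching is a tool for non-randomised groups. Here allocation was random, so any sex or age difference is chance and there is no confounding by treatment choice to remove. If a chance imbalance matters, regression adjustment deals with it and keeps every patient. Matching can only keep or lose patients, and it produces a second estimate of the same effect that depends on the matching settings.

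**Attendance split.** Randomisation balances what patients bring to allocation, not what they do afterwards. Patients know their arm, one arm receives messages that promote recommended behaviour, and rehabilitation is a recommended behaviour. If the app alters who attends, attenders in the two arms are different kinds of patient, and so are non-attenders. A difference within either subset could then reflect selection. The statement that randomisation makes refusal similar is an expectation, not something the design secures. Even equal numbers of refusers would not guarantee comparable patients within each subset.

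**Working it through.** **1. The plan's own figure.** Inputs from Sample size {14}: 50% v 20%, power 80%, significance 5% (two-sided assumed). Per arm, n = [1.96·√(2·0.35·0.65) + 0.842·√(0.25 + 0.16)]² / 0.30² = 38.5. Rounded up this is 39 per arm, or 78; the article gives 38 per arm, or 76. The figure reproduces to within rounding. The target of 100 leaves room for 24 losses.

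**2. Patients left after matching.** The article gives no ratio, caliper or age distribution. Assumed: 1:1 nearest-neighbour matching without replacement on the logit of a propensity score from age and sex; age mean 60, SD 10; 75% men; 100 patients.

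| Allocation | Caliper | Mean pairs | Patients dropped (100 − 2 × pairs) |
|---|---|---|---|
| exactly 50/50 | none | 50 | 0 |
| exactly 50/50 | 0.2 SD | 39.8 | 20.4 |
| simple randomisation | none | 46.0 | 7.9 |
| simple randomisation | 0.2 SD | 38.8 | 22.4 |

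Age SD 11 gives nearly the same under simple randomisation (46.1 and 38.9 pairs). The no-caliper loss is just the surplus of the larger arm: with 100 patients and simple randomisation the arms differ by 8.0 on average, and by 10 or more with probability 0.37. The allocation section describes a list of 100 ones and twos and mentions no blocking, and the stated reason for matching refers to group size, so unequal arms are plausible.

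**3. Power of the matched comparison.** Exact enumeration of Fisher's test at 50% v 20%:

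| Per arm | Power |
|---|---|
| 50 (all randomised) | 0.85 |
| 46 (no caliper) | 0.82 |
| 39 (0.2 SD caliper) | 0.73 |

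**4. Attendance split with an app that does nothing.** The article gives no attendance figures, so these are illustrations. Assumed: a standard normal prognostic factor u; event logit −0.65 + 0.9u in both arms; attendance logit −1.0u in control and −1.0u + 1.0 with the app. Attendance is then 50% v 70%, and the overall event rate is 36.5% in both arms.

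| Subset | Control | App | App − control |
|---|---|---|---|
| Attenders | 29.1% | 31.7% | +2.6 points |
| Non-attenders | 44.0% | 47.3% | +3.3 points |

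The false difference runs against the app in both subsets.

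A second assumed model shows that the pattern depends on the mechanism. With the app raising attendance by 20 points only in poorer-prognosis patients, app v control is 47.6% v 44.1% in attenders and 53.7% v 56.1% in non-attenders, so the two subsets err in opposite directions. With no effect of the app on attendance, both subsets are unbiased.

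**5. Scale of that bias here.** At 50% v 70% attendance with 50 per arm, there are 25 v 35 attenders and 25 v 15 non-attenders. Standard errors of the differences:

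- Attenders: √(0.291·0.709/25 + 0.317·0.683/35) = 0.12, or 12 points.
- Non-attenders: √(0.440·0.560/25 + 0.473·0.527/15) = 0.16, or 16 points.

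Fisher's test at these biased rates rejects 3.7% of the time in attenders and in under 4% in non-attenders, below the nominal 5%.

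**The case against.** Both analyses are presented as additions, so the unmatched comparison of the randomised groups stands and its power is untouched. This is correct and limits the severity.

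A reader might infer that matching will throw away a fifth of the trial and drop power to 0.73. The article does not support that. The figure depends on a caliper that the article does not state and may properly leave to a fuller document. Without a caliper, power stays near 0.82, above the planned 80%, and equal arms would lose nobody. What stands is that matching cannot improve on adjustment in all patients and may do worse.

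A reader might also infer that the attendance split will manufacture a benefit. The article does not support that either. The shift in attendance is assumed. The article expects none, and it attributes some refusals to fear of infection, a motive that may precede allocation. It does not say when patients decide. In the main example the bias is small beside its standard error and disfavours the app. What stands is narrower: attendance is observed after allocation, and nothing in the design guarantees that it is unrelated to arm.

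**Conclusion.** The point holds as a minor to moderate one about two supplementary analyses.

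Matching on sex and age is inferior to covariate adjustment in a randomised trial. Its cost ranges from nothing (equal arms, no caliper) through about 0.03 in power (0.85 to 0.82; simple randomisation, no caliper) to about 0.12 (0.85 to 0.73; simple randomisation, 0.2 SD caliper). These values assume the planned 50% v 20% rates, complete follow-up and the age and sex distribution given above.

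The attendance split does not give protected randomised comparisons, and the article's reliance on randomisation to equalise refusal is not secured by the design. Any bias requires the app to change who attends. Its size and direction cannot be derived from the article; about 3 points against the app is one illustration.

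It would go too far to conclude that the primary result is compromised. Neither analysis replaces it.

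**What to change.** 1. Replace matching with one prespecified adjusted analysis of all randomised patients, for example logistic regression of the primary endpoint on arm, age and sex, reported with a 95% confidence interval. State that it supports the unadjusted comparison. Other adjusted estimators would serve equally well.
2. Report rehabilitation attendance by arm.
3. Label the attended/not-attended split exploratory and descriptive, with no claim of a treatment effect within either subset.
4. In the Intervention description, reword the sentence on refusals so that similar attendance is an expectation to be checked against the data, not a consequence of randomisation.

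Cost: wording only. Sex and age are already collected (text after Table 1), and the planned split already requires attendance to be recorded. An interaction test on intention to attend recorded before allocation would be cleaner, but the article mentions no such variable. With this version dated February 21, 2022 and recruitment due to end on March 31, 2022, it would come too late for most participants, so it is not part of the request.
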